## Abstract

**Background:**

Medication errors, adverse drug events and potential adverse drug events are common and serious in terms of the harms and costs that they impose on the health system and those who use it. Errors resulting in preventable adverse drug events have been shown to occur most often at the stages of ordering and administration. This paper describes the protocol for a pragmatic trial of electronic prescribing to reduce prescription error. The trial was designed to overcome the limitations associated with traditional study design.

**Design:**

This study was designed as a 65-week, cluster randomized, parallel study.

**Methods:**

The trial was conducted within ambulatory outpatient clinics in an academic tertiary care centre in Ontario, Canada. The electronic prescribing software for the study is a Canadian electronic prescribing software package which provides physician prescription entry with decision support at the point of care. Using a handheld computer (PDA) the physician selects medications using an error minimising menu-based pick list from a comprehensive drug database, create specific prescription instructions and then transmit the prescription directly and electronically to a participating pharmacy via facsimile or to the physician's printer using local area wireless technology. The unit of allocation and randomization is by 'week', i.e. the system is "on" or "off" according to the randomization scheme and the unit of analysis is the prescription, with adjustment for clustering of patients within practitioners.

**Discussion:**

This paper describes the protocol for a pragmatic cluster randomized trial of point-of-care electronic prescribing, which was specifically designed to overcome the limitations associated with traditional study design.

**Trial Registration:**

This trial has been registered with clinicaltrials.gov (ID: NCT00252395)

## Background & rationale

A medication error, as defined by the National Coordinating Council for Medication Error Reporting and Prevention (NCCMERP), is a preventable event that may cause or lead to inappropriate medication use or patient harm. Such events may be related to practice, products, procedures, and systems, including prescribing, order communication, product labelling, packaging, nomenclature, compounding, dispensing, distribution, administration, education, monitoring, and use [1].

Medication errors, adverse drug events (ADEs), and potential adverse drug events impose substantial harms and costs on patients and the health system. The largest study [2] of the prevalence of ADEs and potential ADEs suggests rates of 6.5 ADEs and 5.5 potential ADEs per 100 hospital admissions. Of the life-threatening and serious ADEs in this study, 42% were preventable, compared with 18% of significant ADEs. Errors resulting in preventable ADEs occurred most often at the stages of ordering (56%) and administration (34%); transcription (6%) and dispensing errors (4%) were less common.

There are little data available on errors (as distinct from ADEs, which reflect actual harm). In one study [3] of 36 participating inpatient institutions, 605 (19%) of 3216 medication doses were given in error. Seven percent of these errors were found to be potentially harmful to patients. However, this study was designed to capture only dispensing errors and not prescribing errors.

Changing clinical practices in the area of prescribing error has been widely discussed. In general, it is thought that systems changes rather than individual educational interventions will be required to trap errors, and the main solution widely discussed is the use of computerized physician order entry (CPOE).

There is reliable evidence that computerized order entry reduces ADEs, but the systems used to date have all been desktop-based. In a systematic review [4] of well-conducted evaluations (one of which was a randomized trial) of physician order entry systems and a recent Canadian randomized trial, the separate studies showed findings such as 81% decrease in total medication errors, 55% decrease in non-intercepted serious medication errors, 13% decrease in cases of inappropriate dosing and 24% decrease in inappropriate frequency of nephrotoxic drugs, all of which were statistically significant. These are substantial benefits, with a median of 55% improvement. These studies and their resultant benefits were obtained in the inpatient setting, where the sheer intensity of prescribing and complexity of patient condition could be expected to result in much higher levels of error. However, there is no reason to believe that the relative benefit obtained in a high intensity setting cannot also be obtained in a lower intensity one.

All reliably evaluated CPOE systems to date have been desktop computer based, but there is widespread use and acceptance among physicians of PDAs (personal digital assistants), in many roles. Clinicians report that drug information on a PDA improved their access to information and efficiency while reducing their self-perceived error rates [5]. The use of these devices for information retrieval in clinical settings is expected to grow as wireless communication becomes more ubiquitous and as more applications become available [5,6]. During the past decade there has been a growing awareness of several interventions, such as point of care information technology, aimed at promoting safer health care for our patients. As far as we are aware, our study is the first to rigorously evaluate PDA-based prescribing systems in which drug interaction, dosing alerts, and adverse event reporting are fully integrated.

This paper describes the protocol for a pragmatic cluster randomized trial of point-of-care electronic prescribing, which was specifically designed to overcome the limitations associated with traditional study design.

## Methods

This study was approved by both the participating hospital and the University of Toronto research ethics boards. A standing advisory committee provided input into the design and conduct of the study since inception and has continued to meet regularly during the implementation. This trial has also been registered with clinicaltrials.gov (identifier NCT00252395).

### The Intervention

A field-tested Canadian electronic prescribing software package (Drugmagnet, Toronto, Ontario) designed for physician prescription entry with decision support at the point of care was used for this study. A physician, using a battery powered PDA (Palm Pilot or equivalent) selects medications using an error minimising menu-based pick list from a comprehensive drug database, creates specific prescription instructions and then transmits the prescription directly and electronically to a participating pharmacy via facsimile or to the physician's printer using local area wireless technology. Each prescription order is checked against stored evidence-based guidelines and a dosing and interactions database.

### Study population

This trial has been conducted within ambulatory outpatient clinics at an academic health sciences centre in Toronto, Ontario, Canada (August 2005 – October 2006). Both a specialist setting (Rheumatology, Dermatology and Cardiology patients) and a primary care Family Medicine setting were used. There are approximately 40 full-time physicians within these clinics, who see a total of approximately 1000 patients each week.

### Study design

The study was a 65-week, cluster randomized (3:1 allocation ratio), parallel study with time as the element of randomization. The randomization scheme was computer generated by the biostatistics department at the hospital. The unit of allocation and randomization was the 'week'; although the unit of analysis is the prescription, with adjustment for clustering of patients within physicians. All participating physicians were trained to use electronic prescribing software, but only half of the weeks in the study period were allocated as intervention or "on" weeks, during which the software was switched on, and prescribing was carried out electronically.

Physician training consisted of a simple two hour training course and follow-up tutoring where necessary. The Health Informatician on the project used regular check-ins and a help-line pager to ensure that all technical issues were fixed in a timely manner and that any prevalent user errors with regard to the software were addressed. No further training was conducted in order simulate real-world conditions with limited user support.

During control periods all prescriptions were written on paper as per standard practice. During intervention periods or "on" weeks, all prescriptions were to be filled using the PDAs and the electronic prescribing software. The randomization was employed by turning the prescribing software servers in each clinic on and off according to the randomization scheme. A health informatics assistant was responsible for carrying out the randomization and the allocation was kept concealed until midnight on the last day of the previous week. If a physician tried to enter a prescription on his or her handheld on a control or "off" week, the system immediately gave a message that the wireless network was not been detected, and that the software was inaccessible.

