### Sample size and analysis plan

The unit of analysis for this trial is the individual prescription, adjusting for clustering of patients within physicians. Given an estimated intra-class correlation value of 0.05, a minimum of 65 weeks of prescribing is required to have 80% power for a two sided test to detect an absolute decrease of 5% from with a control baseline error rate of 25% with a type I error of 5%.

Descriptive statistics will be calculated for all variables of interest. Continuous measures will be summarized using means and standard deviations whereas categorical measures will be summarized using counts and percentages. The principal outcome measure, total prescribing error using PDA-generated versus written prescriptions, will be assessed using a two sample, two-sided test of proportions. This analysis will be performed on an intention-to-treat basis. All analyses will be carried out using the SAS Version 9.1 statistical program (SAS Institute, Cary, NC, USA).

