## Discussion

This trial will be able to evaluate electronic prescribing in a hospital setting effectively while preserving the benefits of randomization to reduce bias. Its design takes into account the need for internal and external validity, that the results are attributable to the intervention and that they may be applied to general practice. This design is practical and does not interfere with usual physician workflow.

The findings from this trial will provide important information about the role of electronic prescribing in the ambulatory setting for clinicians and healthcare policy-makers in distinguishing.

One of the key decisions that required consideration in the design of this trial was the question of the appropriateness of physician- or cluster-level randomization. Rather than allocating physicians between the two groups using a random process, cluster-level randomized trials allocate groups of participants. In this study we randomized by time periods. The rationale for this randomization scheme is apparent when there is a high risk of heterogeneity between groups and to allow for the participating physicians to serve as their own controls groups.

This study will be the first published randomized control trial designed to evaluate the effectiveness of electronic prescribing in reducing prescription error in an ambulatory setting. Although technology applications related to patient safety and human error reduction are sweeping the healthcare landscape, it is important that we do not fall in to the same trap as our forefathers did with medications and snake oils. It is as important if not imperative to rigorously evaluate these applications in pragmatic, real-world fashion so that we can determine if they are truly effective or more of a hindrance than help. We look forward to adding the results of this trial to the growing body of literature in this area.

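### The stated adjustment is for physicians, but the week is what was randomised, so week-to-week variation shared by physicians is left out of the standard error

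*Protocol article*

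**What the plan says.** All references are to the protocol article.

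- **Randomised unit.** Study design: "The unit of allocation and randomization was the 'week". The Abstract's Methods paragraph says the same.
- **How it was applied.** Study design: "The randomization was employed by turning the prescribing software servers in each clinic on and off according to the randomization scheme". Physicians in a clinic therefore share that clinic's condition each week.
- **Physicians in both conditions.** The Discussion gives as a reason for randomising time: "to allow for the participating physicians to serve as their own controls groups". The Design paragraph of the Abstract and Study design nevertheless call the study parallel.
- **Stated adjustment.** Study design: "although the unit of analysis is the prescription, with adjustment for clustering of patients within physicians". The Abstract: "the unit of analysis is the prescription, with adjustment for clustering of patients within practitioners". Sample size and analysis plan: "The unit of analysis for this trial is the individual prescription, adjusting for clustering of patients within physicians". Week is not named in any of the three.
- **Primary test.** Sample size and analysis plan: the principal outcome "will be assessed using a two sample, two-sided test of proportions".
- **ICC.** Same section: "Given an estimated intra-class correlation value of 0.05", with no statement of whether it applies to week, physician or patient.

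**The concern.** Inference should respect the unit that was allocated. When each physician works in both on and off weeks, stable differences between physicians largely cancel out of the comparison. What remains is whatever makes a whole week better or worse for everyone. If callbacks run high in a given week for a reason that touches all physicians, that week moves one arm as a block. A variance computed at physician level does not register this, because every physician's on-minus-off difference is shifted in the same direction.

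At stake is the primary p-value and its confidence interval. With shared week variation, a null effect could be declared significant well above the nominal 5% rate even if the clustering sentence were followed exactly.

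**Working it through.** **1. Can the plan's own figure show which level was meant?** For 25% versus 20%, two-sided 5% and 80% power, the requirement without clustering is 1094 per arm, 2188 in total at 1:1. Study population gives about 1000 patients a week over about 40 physicians, or 25 per physician-week. Taking one prescription per patient (an assumption):

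- Week as cluster, ICC 0.05: design effect 1 + 999 × 0.05 = 50.95. Weeks needed: 2188 × 50.95 / 1000 ≈ 111. However high the weekly volume, the floor is 2188 × 0.05 ≈ 109 weeks.
- Physician-week as cluster: design effect 1 + 24 × 0.05 = 2.2. Weeks needed: 2188 × 2.2 / 1000 ≈ 5.
- At 3:1 allocation the totals are 2868 to 2960, giving 146 to 151 weeks and 6 to 7 weeks.

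None of these gives the stated 65, so the calculation does not reveal the level of the ICC.

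**2. Type I error when shared week variation is ignored.** With *m* prescriptions a week and shared-week ICC ρ, ignoring the week understates the variance by the factor D = 1 + (m − 1)ρ. A nominal 5% test then rejects with probability 2 × [1 − Φ(1.96/√D)]. The article gives neither ρ nor *m*, so both are varied. One schedule for all clinics is assumed.

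| Week ICC | D, m = 200 | Type I error | D, m = 1000 | Type I error |
|---|---|---|---|---|
| 0 | 1 | 5% | 1 | 5% |
| 0.001 | 1.199 | 7% | 1.999 | 17% |
| 0.005 | 1.995 | 17% | 5.995 | 42% |
| 0.01 | 2.990 | 26% | 10.99 | 55% |

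**3. Does physician adjustment help?** This was simulated with no treatment effect: 65 weeks, 40 physicians, 25 prescriptions per physician-week, base rate 25%, physician ICC 0.05, 1:1 allocation, 2000 runs per scenario.

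| Correlation added | Unadjusted | Physician intercept | Physician cluster-robust | Week-level t-test |
|---|---|---|---|---|
| none (physician ICC only) | 4.3% | 4.6% | 4.9% | 5.0% |
| shared week 0.001 | 17.4% | 18.4% | 17.2% | 4.6% |
| shared week 0.005 | 41.2% | 42.4% | 41.6% | 5.2% |
| shared week 0.01 | 57.6% | 58.4% | 57.8% | 5.1% |
| physician-by-week 0.05, no shared part | 18.0% | 19.0% | 5.0% | 5.6% |
| shared 0.005 plus physician-by-week 0.045 | 44.0% | 45.0% | 27.9% | 5.3% |

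Results at 3:1 are similar. A separate simulation of a physician-level test gave 44% at week ICC 0.005. With 5 prescriptions per physician-week (200 a week, 3:1), the unadjusted and both physician-adjusted tests gave 7 to 8% at shared-week ICC 0.001 and 25 to 26% at 0.01; the week-level test stayed at 5%.

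For the shared component, both physician methods match no adjustment to within about one percentage point in this table. Physician correlation alone does no harm in this design.

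**The case against.** **A reader might infer that physician adjustment is never better than none.** The documents do not support that. They do not say what form the adjustment takes. If part of the week correlation is specific to each physician and a physician cluster-robust variance is used, that part is captured: 5% against 18% when all of it is physician-by-week, and 28% against 44% in the mixed case. With no week correlation nothing is inflated. The point is confined to variation shared across physicians.

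**A reader might take the largest figures as the trial's actual error rate, or read 0.05 as the week ICC.** The article gives no prescription count, only patients seen, and does not assign its ICC to a level. The figures are a range under assumptions.

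**A reader might also infer that the own-control structure goes unused.** That does not follow either: a physician-intercept model would use within-physician information.

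**Schedules may have differed between clinics.** The article does not say. If they did, effects common to all clinics would partly cancel, the randomised unit would be the clinic-week, and the figures above would change.

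**An article leaves analysis detail to the fuller plan.** That is fair for model form, but here a level of adjustment is stated three times, and it is not the level randomised.

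**The plain test of proportions already needs replacing.** True, and accounting for the week repairs both, so they should not be counted as two separate defects. But replacing that test with the stated physician adjustment alone would leave this problem in place.

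**Conclusion.** The point holds in a bounded form. The article states a clustering adjustment at the wrong level: weeks are randomised, physicians contribute to both conditions, and only clustering within physicians is adjusted for. If there is week variation shared by physicians, type I error exceeds 5% by about as much as with no adjustment for that component. Over week ICCs of 0.001 to 0.01, that is about 7% to 26% at 200 prescriptions a week and about 17% to 55% at 1000 a week. These figures assume a single schedule for all clinics, and the volume and week ICC are assumed as well. There is no inflation if the week ICC is zero, but nothing in the article justifies assuming that over 65 weeks. A week-level analysis holds close to 5% throughout.

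**What to change.** In the Abstract, Study design, and Sample size and analysis plan, state that the primary comparison accounts for the randomised week, or for the clinic-week if clinics had separate schedules. Two routes would do this; they are different analyses, and one should be named:

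- include week as a random effect or cluster crossed with physician; or
- compare weekly error rates between on and off weeks.

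Base the degrees of freedom on the number of randomised units. Bring the named test of proportions into line with the choice. State which level the ICC of 0.05 refers to. Describe the design as week-randomised with physicians in both conditions, rather than parallel.

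The cost is wording plus one model term or a simpler summary analysis. It needs the week of each prescription; Data collection says forms were collected weekly. The crossed model also needs the prescribing physician, which the article does not list as a recorded field. The downside is wider intervals if week variation is real.

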### Outcomes

The principle outcome measure was total prescribing error, as measured by the number of call backs received from pharmacists to prescribing physicians offices. These are defined as potential medication errors picked up by the pharmacist at the time the prescription is filled. Rates will be compared between intervention and control weeks. Prescribing errors can take many forms and are of different levels of severity and a single prescription can have several errors and all will be counted. The denominator for total error is the total number of prescriptions and the numerator is the sum of the following types of error:

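### The primary outcome is a mean count of errors per prescription but is tested and powered as a proportion; the binomial variance is too small if prescriptions carry several errors, unless the unnamed clustering adjustment corrects it

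*Protocol article*

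**What the plan says.** All references are to the protocol article.

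- **Outcomes.** The principal outcome is total prescribing error, "as measured by the number of call backs received from pharmacists to prescribing physicians offices". The section says that "a single prescription can have several errors and all will be counted" and defines the ratio: "The denominator for total error is the total number of prescriptions and the numerator is the sum of the following types of error". Three types follow: interactions (all four levels counted), dosing and route errors, and legibility. The comparison is described in terms of rates: "Rates will be compared between intervention and control weeks".
- **Sample size and analysis plan.** The same outcome "will be assessed using a two sample, two-sided test of proportions". The planning inputs are a control error rate of 25%, an absolute fall of 5 percentage points, a type I error of 5% and "80% power for a two sided test". On clustering: "The unit of analysis for this trial is the individual prescription, adjusting for clustering of patients within physicians". No method for that adjustment is named.

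Nowhere is the outcome reduced to whether a prescription has at least one error, and nowhere is a count model named.

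**The concern.** A test of proportions treats each prescription as contributing 0 or 1. Under the definition in Outcomes, a prescription can contribute 2 or more, for example when it is hard to read and also has a dosing problem. The two sections therefore describe different quantities: errors per prescription in one, and the share of prescriptions in error in the other.

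Two things are at stake. First, the article does not settle what a change from 25% to 20% means: 5 fewer errors per 100 prescriptions, or 5 fewer erroneous prescriptions per 100. Second, if the variance behind the principal comparison is binomial, it is understated, which makes p-values too small and intervals too narrow. The planned sample size rests on the same variance.

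**Working it through.** **1. The planning figure.** Inputs from Sample size and analysis plan: 0.25 against 0.20, two-sided 5%, power 80%. The usual formula for two proportions at 1:1 is

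n per arm = [1.96·√(2·0.225·0.775) + 0.8416·√(0.1875 + 0.16)]² / 0.05² = (1.1575 + 0.4961)² / 0.0025 ≈ 1,094 prescriptions before clustering.

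The article reports only a length, 65 weeks. This cannot be rebuilt from the stated inputs, because neither the number of prescriptions per week nor the cluster to which the intra-class correlation of 0.05 belongs is given. That is a separate matter, and nothing below depends on it.

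**2. Direction.** Let X be the number of errors on a prescription, with mean μ. X is a non-negative integer, so X² ≥ X and E(X²) ≥ μ. Hence Var(X) = E(X²) − μ² ≥ μ(1 − μ). Equality holds only if no prescription has more than one error. The binomial variance can therefore be too small for this measure, but never too large.

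**3. Size, by assumption.** The article gives no distribution of errors per prescription. Assume no clustering, μ = 0.25 in both arms, and that a share s of erroneous prescriptions has exactly two errors while the rest have one.

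- Share of prescriptions with any error: q = 0.25/(1 + s)
- Var(X) = q(1 − s + 4s) − 0.0625
- Binomial variance: 0.25·0.75 = 0.1875
- Ratio R = Var(X)/0.1875
- Real two-sided level = 2[1 − Φ(1.96/√R)]

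Example, s = 0.20: q = 0.2083; Var(X) = 0.2083·1.6 − 0.0625 = 0.2708; R = 1.44; level = 2[1 − Φ(1.631)] = 10.3%.

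| Assumption | q | Var(X) | R | Real level |
|---|---|---|---|---|
| s = 2% | 0.245 | 0.197 | 1.05 | 5.6% |
| s = 5% | 0.238 | 0.211 | 1.13 | 6.5% |
| s = 10% | 0.227 | 0.233 | 1.24 | 7.9% |
| s = 20% | 0.208 | 0.271 | 1.44 | 10.3% |
| s = 30% | 0.192 | 0.303 | 1.62 | 12.3% |
| Poisson counts | 0.221 | 0.250 | 1.33 | 9.0% |

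A simulation of 200,000 trials with 1,094 prescriptions per arm and no clustering agrees: 7.8% at s = 10%, 10.4% at s = 20%, and 8.8% for Poisson counts. When each prescription is scored simply as any error or none, the same test gives 4.9%.

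**4. Effect on planning.** With Poisson variance (an assumption), n per arm = (1.96 + 0.8416)²·(0.25 + 0.20)/0.05² ≈ 1,413 before clustering. The like-for-like binomial figure (unpooled variance) is 7.849·0.3475/0.0025 ≈ 1,091. At 1,094 per arm, a test using the correct Poisson variance has power Φ(0.05/√(0.45/1,094) − 1.96) = Φ(0.505) ≈ 69%, not 80%.

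**The case against.** The strongest reply is the clustering adjustment, which is stated in the Abstract, in Study design and in Sample size and analysis plan. If it uses an empirical variance, such as a sandwich estimator, a ratio estimator or cluster-level summaries, the observed spread replaces p(1−p) and extra variation from multiple errors is absorbed. An article may leave that method to the analysis plan. This stands. A reader might infer that the primary test is certainly too liberal, but the document does not support that. It would be so if the adjustment merely inflated a binomial variance by a design effect, because the starting variance would still be too small.

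The second reply is that multiple errors may be rare. Errors are picked up through pharmacist call backs, and the article does not say whether one call about two problems counts once or twice. The statement that all errors count favours twice, but nothing indicates a share of 20% or 30%. This also stands: a reader might take 9% to 12% as the actual error rate, yet those are assumed cases and the range starts close to 5%.

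Third, one might object that trivial interactions weigh as much as serious ones. The article chooses that openly, so it is a matter of preference and not an error in the plan.

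None of these replies reconciles the two sections. Reading the outcome as any error or none would make the test fit, but it contradicts the statement that every error is counted. A robust variance would repair the p-value but would not settle which quantity is estimated.

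**Conclusion.** The stated test and power inputs do not fit the stated primary outcome, and the passages must be reconciled. That part rests on the text alone.

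The effect on type I error is conditional. It arises only if some prescriptions carry more than one error and the unnamed adjustment keeps a binomial variance. Under those conditions the direction is certain, towards false positives. The size is unknown: about 5.6% to 12% for a nominal 5% test across the assumed shares of 2% to 30%, at a mean of 0.25 and ignoring clustering. The fall in power from 80% to about 69% likewise assumes Poisson counts and no clustering.

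Whether the adjustment should be made for week or for physician is a separate issue that this point does not decide.

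**What to change.** Choose one of the following, and record the choice before the arms are compared.

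(a) Define the primary outcome as the proportion of prescriptions with at least one error, and keep total errors as a secondary outcome. This fits a clustering-adjusted test of proportions and the 25% to 20% inputs, read as shares of prescriptions. The plan should confirm that reading: if 25% was meant as errors per prescription, the share with any error is lower (0.192 to 0.245 over the assumed shares above). The cost is that multiple errors on one prescription move to a secondary outcome.

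(b) Keep the sum as primary and analyse it as a rate, with a negative binomial model or a Poisson model with robust variance, the number of prescriptions as offset and an allowance for clustering. Report a rate ratio, and restate the power on the count variance. The cost is a new power statement, probably less favourable than the present one.

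Under either option, name the method of clustering adjustment and say how one call back about several problems is counted. The change is to the wording of the outcome and analysis sections, plus the recalculation of power under (b).
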